### Study outcome measures

Developmental outcomes will be assessed using the PCM-IT in a subset of participants at 12 months of age. The PCM-IT combines both parental report and direct observation to provide a comprehensive evaluation of children’s motor skills, cognition, language, personal and socio-emotional development (Table 2). The PCM-IT assessment was derived from infant assessment tools that were developed and standardized in Kenya including the Kilifi Developmental Inventory (KDI) [41], the Developmental Milestones Checklist, Version 2 (DMC-II) [42, 43] and the Profile of Social-Emotional Development (PSED). The PSED is based in part on the Brief Infant/Toddler Social Emotional Assessment [44] to assess social cognition, independence, emotional lability, maladaptive behavior, and social competence [45]. Items for the DMC were drawn from several published measures, including the Griffiths Mental Developmental Scale for Infants [46] and the Vineland Adaptive Behavior Scale [47].

**Table 2 Tab2:** Protocol for child monitoring assessment

Developmental domain	
Motor	• Evaluation of gross and fine motor skills • Assessed through direct observation and parental report • Example of items/activities that are directly observed: o Head control o Lifting upper body o Reaches out for moving object • Example of items/activities that are evaluated through maternal report: o Sits with/without support o Stands with/without support o Crawls/walks
Cognition	• Evaluation of cognition and executive function subscale • Executive function subscale made up of two tasks: self-control and A-not-B tasks • Assessed through direct and discreet observation • Example of items/activities: o Stacking cubes o Removing cubes from a container o Matching colours o Discretely monitor time until child reaches for desirable object they’ve been asked not to touch
Language	• Evaluation of language development through maternal report or if possible, direct observation • Example of items evaluated: o Repeating strings of vowels o Understands/uses gestures o Understands/uses words
Self help/Adaptive Behaviour	• Independence and adaptive behaviour assessed through maternal report • Example of items evaluated: o Dresses self o Feeding behaviour o Indicates when wet
Social Emotional	• Social items and emotional regulation assessed through maternal report • Example of Social items evaluated: o Recognition of people o Reaction to own name • Example of emotional regulation items evaluated: o Eating habits o Playing behaviour

For the majority of items on the PCM-IT, the child is evaluated on a 4-point rating scheme from ‘0’ to ‘3’ (‘0’ denotes ‘not able’; ‘1’ denotes ‘able to carry out the activity momentarily’; ‘2’ denotes ‘carries out the activity but with limitations’; and, ‘3’ denotes ‘able to carry out the activity with little effort’). For all items related to emotional regulation, frequency of occurrence is scored on a 3-point Likert scale (‘0’denotes ‘never or rarely happens’; ‘1’ denotes ‘happens sometimes’; ‘2’ denotes ‘always happens or most of the time’). The first 12-month PCM-IT assessment is scheduled to take place in November 2015.

Secondary outcomes include all-cause newborn mortality (death within the first 28 days of life), the incidence of omphalitis, severe infection, identified cases of hypothermia and hyperthermia, number of LBW newborns identified, health facility usage, and knowledge, attitude, practice and willingness to pay for neonatal kit (Table 3). Due to the nature of the intervention, blinding was not possible. However, to reduce measurement bias, an independent team that is not involved in the delivery of the intervention collects outcome data.

**Table 3 Tab3:** Primary and secondary outcome measures

Outcome	Definition
Primary Outcome	
Neurodevelopment at 12 months of age	Defined by the development score assigned at 12 months of age as measured by the standardized Protocol for Child Monitoring – Infant and Toddler Version
Secondary Outcomes	
All-cause neonatal mortality	Death from any cause in the first 28 days of life
Incidence of omphalitis	A) None (no redness or swelling); B) Mild (inflammation limited to the cord stump); C) Moderate (inflammation extending to the skin at the base of the cord stump less than 2 cm); or D) Severe (inflammation extending more than 2 cm from the cord stump)
Incidence of severe infection	A) Convulsions; or B) Fast breathing (60 breaths per minute or more); or C) Severe chest indrawing; or D) Movement only when stimulated or no movement at all; or E) Not feeding at all for at least 12 h
Cases of hypothermia and hyperthermia identified	Defined using ThermoSpot: A) Moderate hypothermia: pale green and red face (35 °C to 36 °C) B) Severe hypothermia: black face (<35 °C) C) Hyperthermia: blue face (>=39 °C)
Number of LBW newborns identified	<2500 g at first weighing
Health facility use	Health centre visits to A) Dispensary B) Health Centre C) Subcounty Hospital D) County Hospital E) Coast General Hospital F) Private clinic/hospital
Knowledge, attitudes, practices and willingness to pay for the newborn toolkit	Defined by self-reported data on: A) Use of each kit component B) Purpose of each kit component C) Perceptions on ease of use D) Perceptions on safety and effectiveness of kit E) Willingness to Pay for the kit

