## Methods/Design

### Objective and hypothesis

The primary aim of this study is to determine whether an integrated neonatal survival kit and/or newborn stimulation package, when delivered to pregnant women during their third trimester of pregnancy by volunteer CHWs, improves developmental outcomes at 12 months of age. Through a reduction in severe infections and improved thermoregulatory care in the first month of life, we hypothesize that utilization of the neonatal survival kit will result in an improvement of at least one standard deviation in development at 12 months of age as measured by the Protocol for Child Monitoring – Infant/Toddler version (PCM-IT) assessment. Moreover, we hypothesize that the combination of both the neonatal survival kit and early stimulation messaging will have an additive effect on development. Secondary objectives are: i) to determine if introduction of the neonatal survival kit reduces all-cause neonatal mortality; ii) explore whether use of the kit is effective in reducing the incidence of omphalitis and/or severe infection, improves caregiver ability to identify hypothermia and/or fever through use of ThermoSpot, and improves identification of low birth weight through use of a handheld scale. The study will also determine if the interventions increase appropriate referral to local health facilities. Finally, the study will assess knowledge, attitudes, and practices of mothers with their newborn and their willingness to use the kit and their capacity to pay for it.

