### Interventions and comparator

To facilitate future scale-up efforts, the delivery of each intervention was built into the country’s existing health system infrastructure. CHWs routinely conduct home visits to pregnant women during their third trimester of pregnancy, and post-delivery during the first week of life and again 4–6 weeks post delivery. Specifically, the timing of intervention delivery coincides with the existing schedule of CHW home visits. In this trial, a trained study worker accompanies CHWs to their third trimester home visit, explains the study to potential participants, and seeks informed written consent. After obtaining consent, CHWs deliver the appropriate intervention(s) and corresponding education to enrolled pregnant women. In control clusters, CHWs deliver the current standard of community-based pre-natal care in Kenya [38].

The integrated neonatal survival kit comprises a clean birth kit, 4 % chlorhexidine solution, sunflower oil emollient, ThermoSpot™, Mylar infant sleeve, and a reusable, instant heat pack (Fig. 3). In addition, CHWs in the intervention groups are also supplied with a handheld battery-operated weighing scale with a suspended sling to weigh newborns (Fig. 3). A detailed description of each kit component, its intended utilization and associated evidence has been published elsewhere [39].

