At the first data collection visit, the data collector administers a questionnaire to document the events surrounding delivery and the immediate post-natal status of the newborn, including measurement of newborn weight. At each subsequent visit, data collectors administer a questionnaire covering the events that have occurred since the last visit to assess outcomes in the newborn. Data collectors are not trained to treat outcome conditions; rather, they are trained to identify newborn danger signs and make appropriate referrals. As an extra precaution, data collectors are required to report all newborn danger sign to their direct supervisor who then relays the information to the CHEWs based at their dispensary. On the day 28 visit, data collectors also administer a brief questionnaire to participants enrolled in the kit-only and kit plus stimulation intervention arms to assess participants’ knowledge, attitudes and practice toward the neonatal kit as well as their willingness to pay for the kit. Information on caregiver socio-demographics characteristics is also collected.

If a newborn is not enrolled into the study by day three of life, they are no longer eligible to receive a complete series of data collection visits (days 1, 3, 7, 14, and 28 of life). In these situations, a short questionnaire is administered on day 28 of life to capture information on the pregnancy outcome (i.e., live birth or stillbirth), whether components of the kit were used by participants in the kit-only and kit plus stimulation groups, and in cases of live births, the neonatal outcome (i.e., alive or dead on day 28 of life). In cases where the study team is not aware of the birth of a baby until after day 28 of life, a data collector is dispatched to the home of the participant as soon as the delivery notification is received. If the mother or caregiver is unavailable at the time of this visit, the data collection visit is rescheduled to the earliest available time.

In the event of a newborn death, the parent will be given the choice of participating in a verbal autopsy [13]; a minimum 2-week mourning period precedes the administration of the verbal autopsy. To determine cause of death, two pediatricians will review all completed verbal autopsy forms. If a discrepancy exists in the cause of death ascertained by the two primary reviewers, a third senior pediatrician will act as an adjudicator.

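### Hypothermia, hyperthermia and low birth weight 'identified' lack a common yardstick across arms, so counts compared between arms cannot show improved identification

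*Protocol article*

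**What the plan says.** The protocol article, under Objective and hypothesis, sets an exploratory secondary objective for the kit. One part asks whether it "improves caregiver ability to identify hypothermia and/or fever through use of ThermoSpot". Another asks whether a handheld scale improves identification of low birth weight.

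Table 3 (Study outcome measures) turns these into two outcomes:

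- Temperature cases: "Defined using ThermoSpot: A) Moderate hypothermia", followed by severe hypothermia and hyperthermia, each given as a colour on the same device. No other method of measurement is named.
- Low birth weight: "<2500 g at first weighing". The person weighing and the scale are not named.

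Under Interventions and comparator, the kit contents include "sunflower oil emollient, ThermoSpot™, Mylar infant sleeve, and a reusable, instant heat pack". For scales, "CHWs in the intervention groups are also supplied with a handheld battery-operated weighing scale". For the comparator, "In control clusters, CHWs deliver the current standard of community-based pre-natal care in Kenya".

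Under Data collection and data management, data collectors visit homes in intervention and control clusters alike. At the first visit they record "the immediate post-natal status of the newborn, including measurement of newborn weight". Later visits are described as a questionnaire about events since the previous visit. No temperature reading by data collectors is described.

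**The concern.** Whether identification improves is a comparative question. It needs a measurement made the same way in every arm, against which identification by caregivers or CHWs can be judged. Table 3 instead defines the temperature cases by a device that is itself part of the intervention, and defines low birth weight by a weighing that could be made by either of two people.

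If counts defined in this way are compared between arms, a difference could be reported as better identification when it shows only that one group held the device. Equally, a real benefit of the CHW scale could be invisible because the study team weighed every baby. The kit also contains warming items and is expected to improve thermal care. A raw case count therefore mixes fewer cases (prevention) with more cases found (detection), and these move it in opposite directions.

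**Working it through.** The article states no rate, power or sample size for these two outcomes, so there is no plan figure to reproduce. The check traces what each arm can record, then illustrates the size.

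**Temperature: who can be a case.** ThermoSpot is in the kit, so it is present in the kit-only and combined arms. Control and stimulation-only newborns have no stated route to a reading. There are two possibilities:

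1. Data collectors do not use ThermoSpot in non-kit homes. Under Table 3, non-kit cases are then nil or nearly so, whatever the true incidence.
2. Data collectors use it in all homes. Ascertainment is then equal, but the count is the study team's detections, and the objective concerns the caregiver's.

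**Illustration.** From the article (Sample size and power estimation): target 3000 pairs and a 25 % chance of each arm, so n = 3000 × 0.25 = 750 per arm. Assumed, because the article gives no figures: true incidence equal in both arms at 5, 10 or 20 %; detection 50 % in the kit arm and 0, 10 or 25 % in the non-kit arm; two-sided 5 % test; clustering ignored, so a clustered analysis would give somewhat lower probabilities.

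With p = incidence × detection in each arm and p̄ their mean, the probability of significance is Φ(z), where

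z = [(p₁ − p₂)√n − 1.96√(2p̄(1 − p̄))] / √(p₁(1 − p₁) + p₂(1 − p₂)).

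Worked case: incidence 5 %, detection 50 % v 10 %. Then p₁ = 0.025, p₂ = 0.005 and p̄ = 0.015.

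z = (0.02 × √750 − 1.96 × √0.02955) / √0.02935 = (0.548 − 0.337) / 0.171 = 1.23, so Φ(z) = 0.89.

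Expected counts (kit v non-kit) and probability of a significant difference:

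| Detection, kit v non-kit | Incidence 5 % | Incidence 10 % | Incidence 20 % |
|---|---|---|---|
| 50 % v 0 % | 18.8 v 0; 0.99 | 37.5 v 0; 1.00 | 75 v 0; 1.00 |
| 50 % v 10 % | 18.8 v 3.8; 0.89 | 37.5 v 7.5; 0.995 | 75 v 15; 1.00 |
| 50 % v 25 % | 18.8 v 9.4; 0.43 | 37.5 v 18.8; 0.72 | 75 v 37.5; 0.96 |

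At the extreme of no non-kit readings, six flagged infants in one kit arm (6/750 = 0.8 %) against none gives a two-sided exact p of about 2 × (1/2)⁶ = 0.031. Five against none gives about 2 × (1/2)⁵ = 0.0625.

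**Prevention and detection cancel.** The expected count is n × incidence × detection. Incidence 10 % with detection 25 % gives 750 × 0.10 × 0.25 = 18.75. Incidence 5 % with detection 50 % gives 750 × 0.05 × 0.50 = 18.75. A kit that halved incidence and doubled detection would show no difference.

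**Low birth weight: who weighs first.** Let π be the true prevalence, equal across randomized arms.

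- Data collector's weight: every arm is weighed alike and the expected count is nπ in each. The expected difference is 0, because a CHW scale used after birth cannot change birth weight.
- CHW's weight: control clusters hold no study scale. The count then depends on who was weighed, and no common denominator shows what share of low-weight infants was found.

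Data collectors aim for day 1 or as soon as possible after notification, while the CHW's postnatal visit falls in the first week. The study weighing may therefore often come first.

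**The case against.** The strongest case for the plan is that these are gaps in a condensed article. Table 3 does not say who reads ThermoSpot, and the article sends the intended use of each kit component to a separate publication. Data collectors visit all arms specifically to assess secondary outcomes and might carry the device. The Data analysis plan names survival and related outcomes in the four groups, not temperature or birth weight. Table 3 already holds one outcome collected in the kit arms only (knowledge, attitudes and willingness to pay), so a description within the kit arms would be compatible with the text. If the first weighing is the CHW's, finding more low-weight babies where CHWs have a scale is arguably the very effect a pragmatic trial should measure.

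Much of this stands. A reader might infer that non-kit temperature counts are zero by construction and the result is settled in advance. The article does not support that as a certainty, because it never says that ThermoSpot is absent from non-kit homes. A reader might also infer that the low birth weight outcome can never show a benefit of the scale; that holds only if the data collector's weight is the one meant. Nor is it fully open which arms hold scales. The wording about intervention groups is loose, but the objective and the kit figure both tie the scale to the kit.

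What does not stand is that naming the reader or weigher would be enough. Whichever answer is given, the raw counts do not measure improved identification against a common reference, and the objective is worded comparatively.

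**Conclusion.** The concern holds in conditional form. As defined, ThermoSpot cases compared between arms reflect either device availability or the study team's own detections, and neither is caregiver identification. Low birth weight at first weighing is either prevalence, which the scale cannot alter, or a CHW count without a common reference.

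The size depends on assumed incidence and detection. With equal true incidence of 5 to 20 % and 750 per arm, the chance of a significant difference is 0.99 or higher if non-kit detection is nil, 0.89 to 1.00 at 10 %, and 0.43 to 0.96 at 25 %, each against 50 % in the kit arm. These figures apply only if the counts are tested between arms, which the comparative objective suggests but the analysis section does not state for these outcomes.

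Both items sit within one exploratory secondary objective. The primary outcome and mortality are unaffected.

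**What to change.** - **Temperature.** Do not use ThermoSpot-defined counts compared between arms as evidence of improved identification; report them descriptively within the two kit arms. If caregiver recognition of a cold or hot newborn is to be compared, ask about it identically in all four arms and label it exploratory and self-reported. Without a reference temperature it cannot separate correct from false recognition, and caregivers holding the device may simply report more.
- **Low birth weight.** Take the data collector's first-visit weight as the reference in all arms. Record identification by the CHW or caregiver separately, with its date, because the study weighing may come first. Report the proportion of reference-low-weight infants so identified.
- **Definitions.** Name the weigher in Table 3 and state which arms hold scales.

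The cost is two reworded outcomes and a few questions on existing forms, with no new visits or equipment. There are limits. Recognition is self-reported, and new questions cannot be asked at visits already completed; the first newborn was enrolled in November 2014. The article also describes no weighing for infants not enrolled by day three, who receive only a short day 28 questionnaire, so the reference weight would cover only those enrolled in time.

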### Data collection and data management

Forty data collectors, each with a minimum qualification of high school education level, underwent 3 days of formal training. In this training, the goals of the study were explained to them, they were taught basic methodology, and provided with an in-depth understanding of each data collection form. To assess secondary outcomes, data collectors visit homes in the intervention and control clusters on days 1 (or as soon as possible after birth notification), 3, 7, 14, and 28 of life. Data collection in the first few days of a newborn’s life is critical to the study’s success as many of the secondary outcomes measured in this study may occur very soon after delivery. Data collection visits are considered missed once the next data collection point is reached. For example, the day 7 visit can be completed up to day 13; on day 14, the day 7 visit is considered missed. The day 28 visit is considered missed, if two weeks after the scheduled visit, the questionnaire has still not been completed. To facilitate timely birth notifications, at the time of consent, participants are provided with contact information and instructions to notify the study team and/or their CHWs as soon possible following delivery. Moreover, a small monetary incentive is provided to both participants and CHWs for birth notifications that lead to the enrolment of an infant by day three of life.

At the first data collection visit, the data collector administers a questionnaire to document the events surrounding delivery and the immediate post-natal status of the newborn, including measurement of newborn weight. At each subsequent visit, data collectors administer a questionnaire covering the events that have occurred since the last visit to assess outcomes in the newborn. Data collectors are not trained to treat outcome conditions; rather, they are trained to identify newborn danger signs and make appropriate referrals. As an extra precaution, data collectors are required to report all newborn danger sign to their direct supervisor who then relays the information to the CHEWs based at their dispensary. On the day 28 visit, data collectors also administer a brief questionnaire to participants enrolled in the kit-only and kit plus stimulation intervention arms to assess participants’ knowledge, attitudes and practice toward the neonatal kit as well as their willingness to pay for the kit. Information on caregiver socio-demographics characteristics is also collected.

If a newborn is not enrolled into the study by day three of life, they are no longer eligible to receive a complete series of data collection visits (days 1, 3, 7, 14, and 28 of life). In these situations, a short questionnaire is administered on day 28 of life to capture information on the pregnancy outcome (i.e., live birth or stillbirth), whether components of the kit were used by participants in the kit-only and kit plus stimulation groups, and in cases of live births, the neonatal outcome (i.e., alive or dead on day 28 of life). In cases where the study team is not aware of the birth of a baby until after day 28 of life, a data collector is dispatched to the home of the participant as soon as the delivery notification is received. If the mother or caregiver is unavailable at the time of this visit, the data collection visit is rescheduled to the earliest available time.

In the event of a newborn death, the parent will be given the choice of participating in a verbal autopsy [13]; a minimum 2-week mourning period precedes the administration of the verbal autopsy. To determine cause of death, two pediatricians will review all completed verbal autopsy forms. If a discrepancy exists in the cause of death ascertained by the two primary reviewers, a third senior pediatrician will act as an adjudicator.

At 12 months of age, a subset of children will undergo a standardized assessment of development by a study worker trained in the delivery of the PCM-IT assessment. The study worker will be blinded to the arm of the trial to which the participant was randomized. The assessment will take place in the child’s home in the presence of their primary caregivers and will take approximately 1 h to administer. At the assessment, the study worker will explain and demonstrate each new task before monitoring the child’s attempt at the activity and scoring their abilities. A number of items on the PCM-IT, for example ‘sitting with support,’ will be scored through observing the child’s behavior. Children will receive a score for all 57 assessment items in the checklist and a summated score will be calculated for four areas; gross and fine motor skills, cognition and executive function. In addition, the parental interview covering 46 items will yield scores in four areas: language, self-help/adaptive, social and emotional regulation. The PCM-IT assessment will also be used to measure the baseline developmental score within the study population in a group of children born before this study commenced and thus were not exposed to the kit, stimulation, or other study activities. A questionnaire will be administered to every study participant who receives a developmental assessment to assess various demographic and socioeconomic factors, which may be associated with developmental outcomes.

Data are collected on paper forms in the homes of participants. Completed data forms are transported to local health facilities where they are stored securely until they can be transported to the centralized Data Management Unit (DMU) in Mombasa, Kenya. Each week, paper forms are delivered to the DMU where they are double entered into electronic format by two independent data clerks. Prior to data entry, all forms are checked for completeness and consistency. In case of inconsistency or missing responses, the editors flag the errors/omissions and consult the interviewers for possible explanations. For data entry, databases and entry screens were developed using EpiInfo version 3.5.1. The entry screens employ range and consistency checks to minimize entry of erroneous data.

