### Data analysis plan

Data will be analyzed as intention to treat using univariate and multivariate methods in STATA version 13. PCM-IT scores will be compared using Student’s *t*-test and linear regression models will be used to control for confounders. Survival and other related outcomes in the four groups will be analyzed using Cox proportional hazards analysis. All estimates will be adjusted for cluster allocation according to generalized estimating equation method.

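### The t-test named for the summed PCM-IT scores cannot use exact age at assessment and the regression does not name it, so some precision is given up that a prespecified age term would recover at no real cost

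*Protocol article*

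**What the plan says.** All references are to the protocol article.

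- **Outcome.** Table 3 (Study outcome measures) gives the primary outcome as "Defined by the development score assigned at 12 months of age as measured by the standardized Protocol for Child Monitoring", infant and toddler version. No age-standardised score is described.
- **Scoring.** Under Data collection and data management: "Children will receive a score for all 57 assessment items in the checklist and a summated score will be calculated for four areas". A parental interview of 46 items gives scores in four more areas. For most items, "the child is evaluated on a 4-point rating scheme from" 0 (cannot do it) to 3 (does it with little effort). Emotional regulation items are frequency ratings from 0 to 2. Examples in Table 2 include sitting, standing, crawling or walking, stacking cubes and using words.
- **Timing.** "At 12 months of age, a subset of children will undergo a standardized assessment of development". The same section gives completion windows for the neonatal visits (the day 7 visit may be done up to day 13; the day 28 visit up to two weeks late) but none for the 12-month visit.
- **Analysis.** Under Data analysis plan: "PCM-IT scores will be compared using Student’s" t-test, then "linear regression models will be used to control for confounders". The confounders are not listed. Finally, "All estimates will be adjusted for cluster allocation according to generalized estimating equation method".

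**The concern.** A sum of milestone ratings measures how far a child has progressed, and around 12 months that plausibly changes from month to month. Children seen at 11.5 and 13 months would then differ in expected score whatever their arm. If the analysis does not use exact age, that spread stays in the residual variance and widens the confidence interval for the treatment contrast.

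Some spread is likely. The assessment is a home visit of about an hour with the caregiver present, no window is stated, and the article expects that some births will come to the study team's notice only after day 28.

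At stake is precision for the primary outcome. It matters more if the true effect is well below the 1 SD used for planning, and if the assessed subset, whose size is not stated, is small.

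**Working it through.** **1. The plan's own figure.** Sample size and power estimation claims more than 90% power for a 1 SD difference between any two groups. No alpha is stated; two-sided 0.05 is assumed.

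- n per arm = 2 × (1.96 + 1.282)² / 1² = 21.0, so 22.
- Power with 22 per arm = Φ(√(22/2) − 1.96) = Φ(1.357) = 91.3%.
- With everyone followed: 689 × 5 × 0.9 × 0.9 = 2790, or about 698 per arm, power is essentially 100%.

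The claim reproduces for any subset of at least about 22 effective children per arm.

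**2. Share of variance due to age.** Let the SD at fixed age be 1, the slope b SD per month, and the SD of age at assessment s months. The unadjusted variance is 1 + (bs)², and the removable share is (bs)² / (1 + (bs)²). Both b and s are assumptions.

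| Assumption | bs | Removable share |
|---|---|---|
| b = 0.2, s = 0.5 | 0.10 | 0.01/1.01 = 1% |
| b = 0.4, s = 1 | 0.40 | 0.16/1.16 = 14% |

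A second set takes ages as uniform within ±w months of 12, so that s² = w²/3.

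| b | w | b²w²/3 | Removable share |
|---|---|---|---|
| 0.1 | 0.5 | 0.0008 | 0.1% |
| 0.3 | 1 | 0.030 | 3% |
| 0.3 | 2 | 0.120 | 11% |
| 0.3 | 3 | 0.270 | 21% |

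Large shares need either a steep slope or visits spread over several months.

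**3. Effect on the stated power.** Without age, the required n per arm for 1 SD is 21.0 × (1 + b²w²/3). Over the uniform-age range (b = 0.1-0.3, w = 0.5-3) this runs from 22 to 21.0 × 1.27 = 26.7, so 27. The stated power is untouched.

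**4. Effect for a smaller difference.** As an illustration, take 0.3 SD with 150 per arm and no clustering; neither figure is in the article. With age adjusted, power = Φ(0.3/√(2/150) − 1.96) = Φ(0.638) = 73.8%. Unadjusted, with b = 0.3, it is 72.6% at w = 1 and 63.5% at w = 3.

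**5. Could imbalance in age create an effect?** The shift in the contrast equals b times the difference in mean age. A half-month difference would shift it by 0.10-0.20 SD at b = 0.2-0.4. With s = 1 month and 150 per arm, the standard error of the difference in mean age is √(2/150) = 0.115 month (clustering ignored). Half a month is 0.5/0.115 = 4.3 standard errors, so chance will not produce it; timing would have to differ systematically by arm. A chance imbalance of one standard error shifts the contrast by 0.115 × 0.2 to 0.115 × 0.4, or 0.02-0.05 SD.

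**The case against.** The strongest reply is that this is only a missing covariate list, which a condensed article may leave to the full protocol or analysis plan. The regression may well include age: the text neither names nor excludes it, and it does not say whether the t-test or the regression is primary. Cluster adjustment is already promised for all estimates. All of this stands. A reader might infer that the primary analysis ignores age; the article does not support that.

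A reader might also infer that the treatment contrast is biased. That is not supported either. Clusters are randomised, all children have the same nominal assessment age, the assessor is blinded to arm, and the birth-notification incentive is described without distinction by arm. The article's remarks on distance and poor roads concern residents reaching health facilities and say nothing of tracing by arm.

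Two further cautions are fair. That scores rise with age is inferred from the item content, and the emotional regulation items may not behave that way. The article calls the instrument standardised and derives it from tools standardised in Kenya, so age-referenced scoring is not ruled out, although only summed scores are described.

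What remains is that the article does name a test for its primary outcome, and that test cannot use age. Replacing it with a more precise model is a change to stated text, and so more than a request for a covariate list.

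**Conclusion.** The point holds as a free improvement in precision. It shows neither an error nor a bias. The named t-test on summed scores cannot use exact age, the regression does not mention it, and the 12-month visit has no stated window.

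The variance at stake is about 1-14% with a slope of 0.2-0.4 SD per month and an age SD of 0.5-1 month, and 0.1-3% with a slope of 0.1-0.3 and ages within 0.5-1 month of 12 months. The article gives no slope, no age spread and no subset size, so the gain could be negligible if visits keep close to the first birthday. The claim of more than 90% power for 1 SD stands in every case tried.

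**What to change.** In the Data analysis plan, replace the t-test as the primary PCM-IT comparison with the linear model already planned, fitted by GEE for clustering by CHW, with age in days at assessment as a covariate fixed in advance. The unadjusted comparison can be kept as supportive. Report the mean and spread of age at assessment by arm, so that readers can see whether timing was balanced. Sex and dispensary are optional further covariates.

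The cost is wording. Date of birth and date of assessment should be on file, since visits are scheduled by day of life; this is an inference, and for births notified late the recorded birth date should be checked. The change should be dated and made before outcomes are compared by arm.
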